## Abstract

**Background:**

Family caregivers provide invaluable support to stroke survivors during their recovery, rehabilitation, and community re-integration. Unfortunately, it is not standard clinical practice to prepare and support caregivers in this role and, as a result, many experience stress and poor health that can compromise stroke survivor recovery and threaten the sustainability of keeping the stroke survivor at home. We developed the Timing it Right Stroke Family Support Program (TIRSFSP) to guide the timing of delivering specific types of education and support to meet caregivers’ evolving needs. The objective of this multi-site randomized controlled trial is to determine if delivering the TIRSFSP across the stroke care continuum improves caregivers’ sense of being supported and emotional well-being.

**Methods/design:**

Our multi-site single-blinded randomized controlled trial will recruit 300 family caregivers of stroke survivors from urban and rural acute care hospitals. After completing a baseline assessment, participants will be randomly allocated to one of three groups: 1) TIRSFSP guided by a stroke support person (health care professional with stroke care experience), delivered in-person during acute care and by telephone for approximately the first six to 12 months post-stroke, 2) caregiver self-directed TIRSFSP with an initial introduction to the program by a stroke support person, or 3) standard care receiving the educational resource “Let’s Talk about Stroke” prepared by the Heart and Stroke Foundation. Participants will complete three follow-up quantitative assessments 3, 6, and 12-months post-stroke. These include assessments of depression, social support, psychological well-being, stroke knowledge, mastery (sense of control over life), caregiving assistance provided, caregiving impact on everyday life, and indicators of stroke severity and disability. Qualitative methods will also be used to obtain information about caregivers’ experiences with the education and support received and the impact on caregivers’ perception of being supported and emotional well-being.

**Discussion:**

This research will determine if the TIRSFSP benefits family caregivers by improving their perception of being supported and emotional well-being. If proven effective, it could be recommended as a model of stroke family education and support that meets the Canadian Stroke Best Practice Guideline recommendation for providing timely education and support to families through transitions.

**Trial registration:**

ClinicalTrials.gov: NCT00958607.

## Background

Stroke is a complex medical condition and, as a result, stroke survivors utilize many elements of the health care system including acute, rehabilitation, and community care services. In Canada, an estimated 58% of stroke survivors go directly home after acute care, 19% go to inpatient rehabilitation before going home, and 10% are admitted to long-term care [1]. As many as 50% of stroke survivors returning to the community have difficulties performing every day activities, including bathing, walking short distances, negotiating stairs, housework, meal preparation and traveling [2]. Family caregivers assist stroke survivors with daily activities and navigating health care services [3]. Currently, there is no standard clinical practice to prepare family members for this caregiving role. As a result, caregivers often experience stress and poor mental and physical health [4-6] that can contribute to poor rehabilitation outcomes for stroke survivors [7] or threaten the sustainability of care at home [8,9]. At the same time, health care delivery systems have been criticized for reducing hospital lengths-of-stay [10], for limiting availability of community services [11], and for lacking continuity across services [12]. This increases the demand placed upon family caregivers as they support individuals with considerable disability across fragmented systems of care with very limited support from community resources. To date, programs have been developed to provide stroke-specific information and caregiver training and counseling, but these have had only a small impact on improving caregiver well-being [13]. One possible explanation, for this for which there is emerging evidence, is that these programs do not consider caregivers’ changing needs across the care continuum [14,15]. We developed the Timing it Right (TIR) framework that aims to guide the appropriate timing of specific types of education and support to meet the evolving needs of caregivers [16].

### “Timing it right” (TIR) framework

The “Timing it Right” (TIR) framework promotes an organized approach to developing and evaluating interventions aimed at meeting family caregivers’ changing needs for support [16]. The TIR framework emphasizes family caregivers’ unique support needs for each of five phases as described in Figure 1. The event/diagnosis phase concerns the time surrounding the stroke event and emergency care. This phase ends when the person’s medical condition has stabilized, at which point caregivers enter the second phase, stabilization. The preparation phase occurs when the stroke survivor is preparing for discharge home from inpatient acute or rehabilitation care. The implementation phase concerns the first few months after the stroke survivor returns home and they are adjusting to living in the community. The adaptation phase occurs once they are comfortable living in the home environment and their emphasis shifts to community re-integration.

**Figure 1 F1:**
[figure not shown]
Timing it right framework (Cameron and Gignac, 2008).

The premise of the framework is that careful attention to phase-specific needs for concrete information and strategies will enhance family caregiver preparedness, ease their transitions across the care continuum, and decrease the occurrence of negative outcomes [16] (e.g., burden, depressive symptoms, and other health issues). Ultimately, there will also be enhanced care of the person with stroke. Interventions developed according to the TIR framework target the support provided to caregivers according to their phase in the TIR framework.

Existing caregiver interventions have drawn substantially from research on social support and aim to provide different elements of support including emotional (e.g., providing comfort, listening to problems [17,18]), instrumental (e.g., providing training in problem-solving [19,20]), informational (e.g., providing information about illness and services [18,21-23]), and appraisal support (e.g., providing feedback about their caregiving activities [24]). Therefore, we have placed the TIR framework in this context of social support. Previous research has demonstrated that family caregivers who can draw upon social support will experience better mental health outcomes [25-27]. In addition, support is most beneficial if it is closely matched to an individual’s current needs [28]. This reinforces the need to more closely examine caregivers’ support needs over time and provide support when and where they need it.

### Previous caregiver intervention research

To date, some interventions have been developed to promote caregivers’ adaptation to their caregiving role (see reviews [13,29]). These interventions often provide information about the illness and treatment [18,21,22,30] or about community services [23]. Some provide caregiver counselling [17,18] or training to assist with solving caregiving problems [19,20,31]. In addition, others have proposed changes to the delivery of acute care and inpatient rehabilitation (e.g., early supported discharge [32], integrated care pathways [33]) that may also benefit family caregivers. Some investigators have studied caregiver interventions that cross a portion of the care continuum, most frequently from acute care to the home. These interventions typically begin when the patient is still in acute care and consist of home visits and/or telephone support to continue the intervention in the community [18,20]. Some interventions use trained nurses [20] or family support organizers [18] to deliver the intervention and have demonstrated some benefit in caregiver outcomes (e.g., constant social support). Similarly, telephone support provided by nurse educators for family caregivers has been associated with small improvements in caregiver problem-solving skills, mental health, perception of preparedness, vitality, and social functioning [19,34,35]. Reviews suggest that these interventions result in small improvements in caregiver burden, emotional distress, psychological well-being, and quality of life [29]. Larger improvements in outcomes are observed with interventions that are tailored to individual caregivers’ needs and are psychotherapeutic, psycho-educational, or multi-component in nature [29]. To date, none of these interventions have specifically considered: 1) the appropriate timing of caregiver education and support; and 2) changes in caregivers’ needs as they provide support to stroke survivors moving across the care continuum. Providing caregivers with the support they need when they need it may be of additional benefit.

The appropriate model for intervention delivery across the care continuum is not yet known. In our qualitative research, caregivers indicated a need for one key individual to be available to them to answer questions and provide support as needed while the stroke survivor was in the hospital and after they had returned home [15]. The stroke support programs discussed above used trained nurses [20] or family support organizers [18] to deliver the intervention in person and by telephone [19,34,35]. Other models have focused on providing integrated service delivery to enhance the coordination of care as patients move across the care continuum [12,36-38]. These commonly use a system where one individual (e.g., a case manager [36]) organizes and facilitates a patient’s access to services across the health care system. The common thread of this research suggests we need to have one key individual provide support across care environments.

In addition, some recent research has highlighted the benefits of preparing patients and their family members to self-manage their transitions across care environments [39,40]. By providing family members with education and guidance, the self-management approach can be extended to enable family members to self-direct their learning and support needs across care environments. This second alternative for intervention delivery may be a cost-effective way for caregivers to obtain the information, training and support that they require when they require it.

## Research objectives and hypotheses

The objective of this multi-site mixed methodology single-blind randomized controlled trial is to determine if the TIRSFSP delivered across the care continuum contributes to positive caregiver outcomes. Since this program targets family caregiver support, the primary outcomes of the intervention will be caregivers’ perception of being supported in their caregiving role and improvements in caregiver mental health outcomes (e.g., less depression and more psychological well-being). To determine the impact of the intervention on caregiver outcomes, we will compare two modes of intervention delivery with standard care: 1) repeated contact in person and by telephone with a stroke support person (health care professional with stroke care experience, intervention arm 1); and 2) a self-directed program by the caregiver (intervention arm 2). The specific research hypotheses are the following:

### Hypotheses

1. Family caregivers receiving the TIRSFSP delivered by a stroke support person and the self-directed TIRSFSP will report more perceived support and better mental health than the standard care group.

2. Family caregivers receiving the TIRSFSP delivered by a stroke support person will report more perceived support and better mental health compared to those receiving the self-directed TIRSFSP and standard care.

## Methods

### Trial design

We will conduct a convergent parallel mixed methodology [41], longitudinal, multi-site, single-blind randomized controlled trial. As a convergent parallel mixed methodology design, the quantitative and qualitative portions of the study will provide different but complementary perspectives on caregivers’ experiences with support received [41]. Recruitment will take place in 7 acute care hospitals from across Canada. Caregivers will be recruited during the patients’ acute care hospital admission. They will complete baseline assessments prior to randomization and follow-up assessments at 3, 6, and 12-month’s post stroke. All caregivers will provide written informed consent. The research protocol has been approved by institutional research ethics boards at all participating hospitals, including the following: University Health Network Research Ethics Board, Capital Health Research Ethics Board, Ottawa Hospital Research Ethics Board, University of Toronto Office of Research Ethics, University of Calgary Faculty of Medicine Office of Medical Bioethics Conjoint Health Research Ethics Board, Pembroke Regional Hospital Research Ethics Committee, Thunder Bay Regional Health Sciences Centre Research Ethics Board, Lakeridge Health Research Ethics Board, Queen’s University Health Sciences & Affiliated Teaching Hospitals Research Ethics Board, Health PEI Research Ethics Board, Royal Victoria Hospital Research Ethics Board, and Cape Breton District Health Authority Research Ethics Board.

### Participants

Family caregivers are defined as the person primarily responsible for providing and/or coordinating stroke survivor care in the community without financial compensation. If during acute care there appears to be more than one family caregiver, we will invite the family member who, in discussion with the family, is likely to be primarily responsible for providing and/or coordinating care in the home.

#### Inclusion criteria

Participants will be included if they are able to read and speak English and will be caring for a person who is either receiving care for their first hospitalization for an ischemic or hemorrhagic stroke or whose previous stroke was mild and they did not require admission to inpatient or outpatient rehabilitation care. The stroke survivor’s anticipated ultimate destination after discharge is a private residence or apartment building. Stroke survivors must exhibit at least minimal disability (i.e., referred to an occupational therapist, physical therapist, or speech language pathologist during acute care). Stroke survivors may be admitted to short or long-duration inpatient (maximum duration of 6 months) or outpatient rehabilitation or return directly home. During inpatient rehabilitation, there will be stroke survivors who do not reach their rehabilitation goals and will, therefore, not be able to return home. When this occurs, we will exclude their caregivers from the study.

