#### Exclusion criteria

We will exclude caregivers of patients who are terminally ill, discharged to alternative levels of care, or discharged to long-term care or assisted retirement residences.

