### Statistical methods

#### Analysis of quantitative data

We will analyze the data on the principle of intention to treat. Hierarchical linear modeling for longitudinal data will examine changes in caregiver outcomes over the follow-up period and examine differences between study groups for each outcome [65]. We will use mixed effects modeling as it accounts for the underlying heterogeneity between and within participants (i.e., intercepts and slopes are allowed to vary across participants). This approach will also allow us to identify differences in rates of change (slopes) in the dependent variables between study groups (e.g., participants in the intervention group with a support person may have earlier improvements in stroke-related knowledge). It will also allow us to control for confounding variables that can also influence caregiver outcomes (e.g., stroke severity). Because intercepts and slopes are computed for each participant, caregivers who miss a follow-up assessment or drop out of the study are still included in the data analyses.

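### Caregivers are excluded after randomisation when the survivor cannot go home from inpatient rehabilitation, which conflicts with intention to treat and may select on an effect of the programme

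*Protocol article*

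**What the plan says.** Under Trial design: "Caregivers will be recruited during the patients’ acute care hospital admission". Baseline assessment comes before randomisation, and under Randomization the data system allocates the arm from the entered baseline record. Under Interventions, the support-person arm begins in person during acute care, and the self-directed arm has its one meeting in the acute phase.

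The Inclusion criteria require that the survivor is expected to end up in a private home. They continue: "Stroke survivors may be admitted to short or long-duration inpatient (maximum duration of 6 months) or outpatient rehabilitation or return directly home". Then: "During inpatient rehabilitation, there will be stroke survivors who do not reach their rehabilitation goals and will, therefore, not be able to return home". For these caregivers the rule is: "When this occurs, we will exclude their caregivers from the study".

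The Exclusion criteria also rule out caregivers of patients "discharged to alternative levels of care, or discharged to long-term care or assisted retirement residences", without saying when this is judged.

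Under Analysis of quantitative data: "We will analyze the data on the principle of intention to treat". The section adds that "caregivers who miss a follow-up assessment or drop out of the study are still included in the data analyses". It says nothing about caregivers whom the protocol itself removes.

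**The concern.** A randomised comparison is protected only while the people compared are those who were randomised. Here membership of the study depends on something that happens weeks or months after allocation, namely whether the survivor gets home. If the programme changes that probability, or changes which survivors fail, the caregivers who remain in each arm are no longer comparable. A difference between arms could then partly reflect who was removed. This bears on all three pairwise contrasts, for perceived support and for the mental health outcomes. Outcomes that are not collected after exclusion cannot be recovered at the analysis stage.

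**Working it through.** **1. Order of events.** Recruitment, baseline, allocation and the first intervention contact are all tied to acute care. Inpatient rehabilitation follows acute care. The exclusion sentence is therefore not a screening rule. Screening on expected destination is a separate sentence in the same section.

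**2. The two rules side by side.** The Inclusion criteria take a randomised caregiver out of the study because of a post-baseline event. The analysis section promises analysis as randomised and retention of those who miss visits or drop out. Nothing there extends that retention to caregivers removed by protocol.

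**3. Could the event depend on arm?** The Background states that caregiver stress and ill health can worsen survivors' rehabilitation outcomes. The Discussion expects better-supported caregivers to contribute more to recovery and rehabilitation. A dependence is therefore plausible on the document's own argument, though not shown.

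**4. What is lost.** Inpatient rehabilitation may last up to 6 months, and assessments fall at 3, 6 and 12 months after stroke.
- Excluded before 3 months: only baseline exists.
- Excluded between 3 and 6 months: the 6- and 12-month outcomes are missing.
- Excluded after 6 months: the 12-month outcome is missing.

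**5. Illustrative size.** The protocol has no exclusion rate to reproduce. The only input from the document is the SD of 20.8 (Sample size). All rates and gaps below are assumptions.

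Let a fraction p of an arm be excluded, and let retained caregivers score G SD above excluded ones. Write R for the retained mean and μ for the whole-arm mean. Then μ = (1 − p)R + p(R − G), so R = μ + pG. With no true effect and the same G in both arms:

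shift (intervention − control) = (p_int − p_ctl) × G × 20.8

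| Excluded, control | Excluded, intervention | G = 0.3 | G = 1.0 |
|---|---|---|---|
| 10% | 10% | 0 | 0 |
| 10% | 5% | −0.31 | −1.04 |
| 15% | 5% | −0.62 | −2.08 |
| 10% | 15% | +0.31 | +1.04 |

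The 15% versus 5% case at G = 1.0 is (0.05 − 0.15) × 1.0 = −0.10 SD, and −0.10 × 20.8 = −2.08 points.

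If the 1 SD deficit is instead measured from the whole-arm mean, the retained mean rises by p/(1 − p). This gives 0.05/0.95 − 0.15/0.85 = 0.053 − 0.176 = −0.124 SD, or −2.6 points. That version implies a larger gap between retained and excluded caregivers: 1/0.95 = 1.05 SD and 1/0.85 = 1.18 SD.

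The signs reverse if excluded caregivers score higher than retained ones.

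For scale, 100 per arm with a two-sided 0.05 test, 80% power and no multiplicity adjustment detects (1.960 + 0.842) × √(2/100) × 20.8 = 8.2 points between two arms. This benchmark is calculated here; the protocol does not state it.

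**The case against.** **Exclusion may mean only that follow-up stops.** The text does not say that collected data are discarded, and the mixed model keeps people with incomplete data. A reader might infer that excluded caregivers vanish from the analysis and that the analysed number falls well below 300. The document does not establish that. But the milder reading does not remove the problem. Later outcomes are still missing because of a post-randomisation event, and someone excluded before 3 months contributes no follow-up. The model would in effect fill the gap from caregivers with a similar history whose survivors were not excluded.

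**The detail may lie elsewhere.** The full protocol, any analysis plan and the participant-flow figure are not shown, and analysis-set definitions are often left to them. That would excuse silence. Here, however, two stated rules conflict.

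**The Exclusion criteria may be pure screening.** A reader might infer that they too operate after randomisation. They can equally be read as applying before it, so they are ambiguous and the point does not rest on them.

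**The causal route is thin.** The Background's remark that caregiver strain can "threaten the sustainability of care at home" most naturally concerns care after the survivor is home, so it does not support the point. The statement about rehabilitation outcomes does. The support person's calls are described as following discharge home, with no clear contact during inpatient rehabilitation, so a large difference between arms is speculative.

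**Other inferences that do not stand.** A reader might infer that the most burdened caregivers are the ones removed. The rule selects on the survivor's recovery, and nothing links that to low perceived support. A reader might also infer that the trial becomes underpowered. The protocol gives its effect only as medium; at 0.5 SD, 63 per arm would suffice and 85 per arm would still give 90% power. Avoiding institutional care is not among the objectives, so failing to measure it is no defect.

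**The target is caregivers at home.** This is true, but the expected-destination criterion already selects for that before randomisation.

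**Conclusion.** The point holds for the inpatient-rehabilitation sentence in the Inclusion criteria. It is a post-randomisation exclusion, it conflicts with the intention-to-treat statement, and on the protocol's own rationale the excluding event may depend on allocation. The arm contrasts can therefore be biased in either direction.

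The size is unknown. Under the assumed rates and gaps, the shift is at most about 2.1 points (2.6 if the gap is taken from the whole-arm mean), and it is zero when rates and gaps are equal across arms. That is modest beside the 8.2-point benchmark. The figures also apply to the reading in which excluded caregivers leave the analysis; if earlier data are kept, the bias depends on how well the model stands in for the missing outcomes. The case for change rests on the conflict and on the irrecoverable loss of outcomes, not on a demonstrated large bias.

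**What to change.** Reconcile the Inclusion criteria, the Exclusion criteria and the analysis section as follows:

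- Apply destination criteria only to what is known or anticipated before randomisation, and say so explicitly in the Exclusion criteria.
- Continue the 3-, 6- and 12-month assessments for every randomised caregiver who consents, wherever the survivor ends up, and analyse all as randomised.
- Report by arm how many survivors did not return home, and when.
- Keep the returned-home subset only as a labelled sensitivity analysis.

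Stating that collected data are kept and reporting exclusions by arm, or defining non-return home as an intercurrent event with a stated strategy, would resolve the wording. Neither recovers the outcomes unless assessment also continues.

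The cost is a change of wording and continued questionnaires for these caregivers. Some items on caregiving assistance and impact apply less when the survivor is in a facility, and the sample becomes slightly more heterogeneous. Perceived support, depression and positive affect remain measurable.
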